#### Screening

Following admission to the recruiting unit/service, the patient’s UC team will work closely with experienced and appropriately trained Clinical Research Network (CRN)/local research staff to screen out clearly ineligible patients. The patient’s UC will also provide detailed information about the eligibility criteria for participation in the trial, and will generate a list of potentially eligible participants to track throughout admission and up to 12 weeks post-stroke. Anonymised screening logs will be completed and returned to the Clinical Trials Research Unit (CTRU) regularly to aid identification of recruitment issues.

#### Recruitment in hospital

Recruitment posters with contact details of research staff will be displayed at each site. The UC team will obtain verbal consent from potentially eligible participants to be approached by a researcher. Research staff will approach the patient (and carers if appropriate) and discuss study participation. Those showing interest will be given verbal and written study information, and opportunities to ask questions. They will be asked if they have a carer they wish to nominate, and provided with carer involvement information if appropriate.

The time period given for decisions to participate will vary according to hospital length of stay, and appropriate confirmation of eligibility, written informed consent, and completion of baseline assessments will be completed whilst the patient is still an inpatient.

#### Recruitment post-hospital discharge

Patients expressing interest in the study, who have provided consent to be followed up (by completion of the consent to follow-up leaflet), may be discharged from hospital prior to consent and baseline data collection. In these instances, they will be contacted by research staff to arrange a visit at the patient’s home or hospital to discuss the study further, confirm eligibility, obtain informed consent, and complete the baseline assessments.

In instances where patients were not approached during their hospital stay, their UC team will review their hospital notes for eligibility. Potentially eligible participants will be sent a consent to follow-up leaflet, covering letter, and study information, and asked to complete and return the leaflet within 2 weeks if interested.

Research staff and PIs (or nominees) across inpatient and community settings will be responsible for answering questions, confirming patients’ eligibility, obtaining consent, and performing the baseline assessment.

#### Carer recruitment

Carers will not be approached unless they have been nominated by a participant, and the participant has given verbal consent for them to be approached. Once written informed consent has been obtained from the carer, research staff will arrange to meet them within 2 weeks to perform the baseline assessment.

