### Objectives {7}

The primary objective of this study is to establish whether ESSVR (plus UC) is more effective than UC alone for improving participants’ self-reported RTW (≥ 2 h per week) at 12 months post-randomisation.

The secondary objectives include the following:
To investigate whether the intervention leads to improvement in self-reported work outcomes, including (a) RTW with the same employer, (b) number of hours worked per week, and (c) number of days worked.To investigate whether the intervention improves mood, physical function, participation, health-related quality of life, work self-efficacy, and post-stroke confidence.To determine whether the intervention changes overall health (including accident and emergency visits, inpatient admissions, outpatient visits, and primary care use including medications) and social care resource use.To estimate the likely cost-effectiveness of the intervention compared to UC alone, from the perspective of the NHS and Personal Social Services (PSS).To establish whether the intervention reduces carer burden.

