#### Approach and informed consent of carers

During recruitment or at the baseline assessment, consenting participants will be asked if they wish to nominate a carer to participate in the study. Carers will only be approached if they have been nominated, and the participant has verbally consented to them being approached. Nominated carers will be provided with a study information sheet (Additional file 5) (with covering letter and consent to follow-up leaflet if sent to their home address) informing them about the study. Research staff will meet with interested carers to answer any questions, and obtain written informed consent (Additional file 6).

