### Participant timeline {13}

A participant timeline was created according to SPIRIT guidance [34] and is presented in Fig. 1. Following admission into a stroke service, screening, informed consent, and baseline assessments will be completed within 12 weeks of stroke onset, prior to randomisation and allocation. The ESSVR intervention will commence within 2 weeks post-randomisation, and last as long as needed up to 12 months post-randomisation. The start and end dates within the UC control group will likely vary, dependent on the usual NHS rehabilitation provided by each stroke service. Self-reported follow-up questionnaires will be completed by all participants and nominated carers at 3, 6, and 12 months post-randomisation.

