### Concealment mechanism {16b}

An automated email will be sent from the CTRU 24-h randomisation service to research staff performing the randomisation and the designated RETAKE OTs, confirming randomisation and the participant’s allocation. The site PI will receive an automated email informing them that the participant has been randomised, but no allocation details will be revealed. Participants’ allocation details will only be revealed to PIs following confirmation of the participant’s eligibility, informed consent, and collection of their baseline data.

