## Assignment of interventions: blinding

### Who will be blinded {17a}

Participants and the OTs delivering the intervention will not be blind to allocation group. To minimise the risk of detection bias, baseline data will be collected prior to participant randomisation. Where possible, research staff will be blinded to allocation when they contact participants who have not returned postal/online follow-up questionnaires (following reminder letters/emails).

GPs and the wider health and social care teams will be blinded to participants’ allocation status. ESSVR-directed contact with the GP and wider care teams is permitted as part of the intervention. All reports to the Trial Management Group (TMG) and TSC will be presented in blinded formats.

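### The carer baseline is timed from carer consent and not expressly tied to randomisation, so it can fall after allocation is known and ESSVR has begun

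*Protocol article*

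**What the plan says.** Objectives {7} lists, among the secondary aims, "To establish whether the intervention reduces carer burden". Table 1 schedules the carer measures (Modified Caregiver Strain Index, EQ-5D-5L, resource use, impact on the carer's work) at baseline, 3, 6 and 12 months. It places carer consent in the Screening column.

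Two general statements put baseline before randomisation. Who will be blinded {17a} says "To minimise the risk of detection bias, baseline data will be collected prior to participant randomisation". Participant timeline {13} says that, after admission to a stroke service, "screening, informed consent, and baseline assessments will be completed within 12 weeks of stroke onset, prior to randomisation and allocation".

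The carer-specific steps are elsewhere. Approach and informed consent of carers says "During recruitment or at the baseline assessment, consenting participants will be asked if they wish to nominate a carer to participate in the study", and allows the carer information to go by post, "with covering letter and consent to follow-up leaflet if sent to their home address". Carer recruitment then says that, after written carer consent, "research staff will arrange to meet them within 2 weeks to perform the baseline assessment".

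On what follows randomisation, Participant timeline {13} says "The ESSVR intervention will commence within 2 weeks post-randomisation". Implementation {16c} has the RETAKE OT tell ESSVR participants their allocation and the trials unit write to usual-care participants. Concealment mechanism {16b} sends the allocation by automated email to the OTs and to the research staff who carried out the randomisation. It withholds allocation from the site PI until the participant's eligibility has been confirmed, together with "informed consent, and collection of their baseline data".

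**The concern.** The only timing rule written for carers starts its clock at carer consent and does not mention randomisation. Carer consent may itself come late, because nomination can happen at the participant's baseline assessment, which is the last participant step named before randomisation. A site that follows these steps as written could randomise the participant while the carer has not yet consented or been assessed.

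Carer burden is self-reported. Participants are told their allocation, and ESSVR includes educating families, so a carer can be expected to know the arm. A value labelled baseline but given at that point may already reflect relief, disappointment or early contact with the intervention, and these differ by arm. If the carer analysis adjusts for it, part of the effect may be removed or bias added. Carers who decide whether to take part once the arm is known may also differ between arms. Analysts cannot reliably repair either problem afterwards.

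**Working it through.** The plan states no figure to reproduce. The check sets the rules side by side and counts days.

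**Does any rule tie the carer baseline to randomisation?**

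- *Carer recruitment*: 2 weeks, counted from carer consent. Randomisation is not mentioned.
- *Approach and informed consent of carers*: nomination as late as the participant's baseline assessment, with a postal route. No deadline relative to randomisation.
- *Participant timeline {13}*: baseline before randomisation. The sentence starts from admission and is bounded by 12 weeks from stroke onset, so it describes patients. The same section names nominated carers expressly when it turns to follow-up.
- *Who will be blinded {17a}*: baseline data before participant randomisation. Carers are not named, but the wording is broad enough to include them.
- *Concealment mechanism {16b}*: lists the participant's own items only, and governs disclosure to the PI, not the act of randomising.
- *Table 1*: carer consent under Screening and carer measures under Baseline. This indicates the intended order but does not say that randomisation waits.

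**Day count.** Assumption: the participant is randomised on day 0, directly after their own baseline assessment. No section requires this or forbids it. Let the carer consent on day c, which the article does not give.

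Latest carer baseline allowed by Carer recruitment = c + 14.

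| Carer consent, day c | Latest carer baseline |
|---|---|
| 0 | 0 + 14 = day 14 |
| 7 | 7 + 14 = day 21 |
| 14 | 14 + 14 = day 28 |

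ESSVR may start on any day from 0 to 14, and the allocation email follows randomisation. In each row the carer baseline can therefore come after allocation is known and after ESSVR has started.

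The carer window by itself guarantees a baseline by day 0 only if c + 14 ≤ 0, that is, if the carer consented at least 14 days before randomisation. A carer first nominated at a baseline visit on day 0 cannot meet that.

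**If the blinding sentence covers carers**, the carer baseline must fall on or before day 0 and the problem does not arise. The 2-week allowance would then need to say that it ends at randomisation, which it does not.

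**Who takes the late baseline.** Research staff meet the carer, and the research staff who carry out the randomisation receive the allocation email. Where they are the same people, both the respondent and the person administering the form may know the arm.

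**The case against.** The strongest reply is that the rule already exists. The blinding sentence is not limited to participants' data: the word participant there describes the randomisation. Table 1 puts carer consent at Screening and carer measures at Baseline, in the same columns used for participants. Carers can also be raised at the first in-hospital approach, so nomination at the baseline visit is the later of two routes. The 2-week window can run entirely before randomisation, and the overlap above needs an early randomisation that no section states. The article condenses a fuller protocol, and its timeline figure is not available here.

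Much of this stands. A reader might infer that nothing at all holds randomisation for the carer baseline. The documents do not support that, given the blinding sentence and Table 1. Nor can the list in Concealment mechanism {16b} be read as the conditions for randomising. A reader might also infer that most carers are affected, or that the carer comparison is invalid. No figure supports the first. The second would need a post-allocation baseline actually to occur and to matter in the analysis, and the article specifies no carer model.

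The reply does not dispose of the point. The article does more than omit a detail: it states a carer-specific window and ties it to an event other than randomisation. If the general rule covers carers, the window does not respect it. If it does not, the stated protection against detection bias is absent for carers. Either way the sections need reconciling.

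**Conclusion.** The point holds as an unreconciled ambiguity with a practical consequence. The article intends baseline data to precede randomisation, but its carer steps do not secure this. On their wording, carer consent and the carer baseline can follow disclosure of allocation and the start of ESSVR, by up to day 14, 21 or 28 for carer consent on day 0, 7 or 14.

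This rests on randomisation soon after the participant's baseline and on the carer-specific wording being followed literally. The share of carers affected and the size of any bias cannot be derived from the article. Only the carer objective is at risk; the participant baseline and the primary outcome are unaffected. It is worth correcting because the objective depends on self-report by people likely to know the allocation, and because the fault cannot be mended at analysis.

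**What to change.** Reconcile Approach and informed consent of carers, Carer recruitment, Participant timeline {13}, Who will be blinded {17a} and Table 1 with one rule: where a carer is nominated, carer consent and the carer baseline booklet are obtained before the participant is randomised. Table 1 already allows self-completion, so the booklet can be filled in at the meeting where the carer consents. Add a short cap, set by the trial team, after which the participant is randomised without waiting, so that participant entry is not delayed. Date every carer form, and do not treat one completed after randomisation as a baseline value.

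The cost is a small change to the carer procedure and the randomisation checklist. The downside is that a few slow-responding carers will have no usable baseline. Whether carers who consent after randomisation are left out of the main carer comparison is a choice for the SAP and not part of this fix.

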## Assignment of interventions: allocation

### Sequence generation {16a}

Participants will be individually randomised to ESSVR (plus UC) or UC alone with a 5:4 allocation ratio. The increased proportion allocated to the intervention arm accounts for a greater level of correlation anticipated in the outcomes for those receiving ESSVR, due to participants being treated by the same OT staff. A 24-h computer-generated minimisation programme will be used for allocation, with incorporation of a random element stratified by site, participant age (< 55, ≥ 55), and stroke severity (derived from EQ5D mobility question and Oxford Cognitive Screen (OCS) picture naming and executive tasks).

### Concealment mechanism {16b}

An automated email will be sent from the CTRU 24-h randomisation service to research staff performing the randomisation and the designated RETAKE OTs, confirming randomisation and the participant’s allocation. The site PI will receive an automated email informing them that the participant has been randomised, but no allocation details will be revealed. Participants’ allocation details will only be revealed to PIs following confirmation of the participant’s eligibility, informed consent, and collection of their baseline data.

### Implementation {16c}

The automated email from the CTRU will detail participant identifiers, randomisation allocation, and subsequent actions required. RETAKE OTs will attempt to contact ESSVR participants to inform them of their allocation; they will also keep a record of participants allocated to UC to ensure RETAKE OTs do not treat UC participants.

UC participants will be notified by CTRU of their allocation via letter, with details of subsequent actions (e.g. follow-up assessments). The CTRU will inform participants’ GPs of study participation via letter, omitting allocation details.

## Assignment of interventions: blinding

### Who will be blinded {17a}

Participants and the OTs delivering the intervention will not be blind to allocation group. To minimise the risk of detection bias, baseline data will be collected prior to participant randomisation. Where possible, research staff will be blinded to allocation when they contact participants who have not returned postal/online follow-up questionnaires (following reminder letters/emails).

GPs and the wider health and social care teams will be blinded to participants’ allocation status. ESSVR-directed contact with the GP and wider care teams is permitted as part of the intervention. All reports to the Trial Management Group (TMG) and TSC will be presented in blinded formats.

### Procedure for unblinding if needed {17b}

If requested by the TMG or TSC (e.g. due to safety concerns), CTRU will provide the relevant allocation status. Where unforeseen unblinding occurs, site staff will provide the CTRU with detailed information on circumstances surrounding the incident.

## Data collection and management

### Plans for assessment and collection of outcomes {18a}

The planned timepoints and methods for outcome data collection are summarised in Table 1.

**Table 1 Tab1:** The planned timepoints and methods for outcome data collection

Assessment	Type	Method of completion	Timeline				
			Screening	Baseline	3 months	6 months	12 months
**Participant data**							
Screening (demographics/assessment of eligibility)	CRF	Researcher	X				
Consent	Consent form	Self-completion	X				
Eligibility/location of baseline assessment	CRF	Researcher		X			
Demographics (age/gender/ethnicity/relationship status/home circumstances/employment details/educational level/driving status)	CRF	Researcher		X			
Oxford Cognitive Screen (OCS)	CRF	Researcher		X			
Details of stroke	CRF	Researcher		X			
Relevant co-morbidities/medical issues	Questionnaire booklet	Researcher/self-completion		X	X	X	X
Contact details (e.g. address/telephone numbers/preferred method of contact/GP details/employer details)	CRF	Researcher		X			
Change of contact details	CRF	Researcher/OT/CTRU		Unscheduled (as made aware)			
Work status	Questionnaire booklet	Researcher/self-completion		X	X	X	X
Hospital Anxiety and Depression Scale (HADS)	Questionnaire booklet	Researcher/self-completion		X	X	X	X
Nottingham Extended Activities of Daily Living (NEADL)	Questionnaire booklet	Researcher/self-completion		X	X	X	X
Community Integration Questionnaire (CIQ)	Questionnaire booklet	Researcher/self-completion		X	X	X	X
Health-related quality of life (EuroQol EQ-5D-5L)	Questionnaire booklet	Researcher/self-completion		X	X	X	X
Resource use (primary care/secondary care/emergency care/medications/social services/wider societal costs (e.g. productivity costs, out of pocket costs))	Questionnaire booklet	Researcher/self-completion		X	X	X	X
Work self-efficacy (single question from the Work Ability Index)	Questionnaire booklet	Researcher/self-completion		X	X	X	X
Confidence after Stroke Measure (CASM)	Questionnaire booklet	Researcher/self-completion		X	X	X	X
Safety reporting	Questionnaire booklet/CRF	Researcher/self-completion			X	X	X
Work status (DWP)	Routine data	Data transfer DWP > CTRU		Downloads to be agreed with DWP to allow 12-month data collection			
Usual care data	CRF	Researcher/self-completion		X	X	X	X
**Carer data**							
Consent	Consent form	Self-completion	X				
Eligibility	CRF	Researcher		X			
Contact details (address/telephone numbers/preferred method of contact/GP details)	CRF	Researcher		X			
Carer demographics (age/gender/ethnicity/relationship to participant/employment details)	Questionnaire booklet	Researcher/self-completion		X	X	X	X
Modified Caregiver Strain Index (MCSI)	Questionnaire booklet	Researcher/self-completion		X	X	X	X
Health-related quality of life (EuroQol EQ-5D-5L)	Questionnaire booklet	Researcher/self-completion		X	X	X	X
Resource use (health, social care, and personal costs)	Questionnaire booklet	Researcher/self-completion		X	X	X	X
Questions relating to impact on carer’s work	Questionnaire booklet	Researcher/self-completion		X	X	X	X

Secondary outcomes not pertaining to work status or days/hours worked will be measured using the following assessment tools:
Mood, measured via the Hospital Anxiety and Depression Scale [41] which has been shown to have excellent internal consistency and construct validity among stroke survivors [42].Functional ability, measured via the Nottingham Extended Activities of Daily Living index [43]. This tool measures abilities to carry out instrumental activities of daily living and has established validity among stroke survivors [44].Social participation, measured via the Community Integration Questionnaire [45]. This tool is designed to assess productivity, and home and social integration following acquired brain injury, and has been found to have acceptable internal consistency [46].Health-related quality of life, measured via the EuroQol EQ-5D-5L [47] which records self-ratings of health relating to mobility, self-care, usual activities, pain/discomfort, and anxiety/depression. It has been shown to have construct and convergent validity when tested on a stroke survivor population [48].Health and social care resource use, measured via a bespoke resource use questionnaire.Work self-efficacy, measured via a single question from the Work Ability Index [49], ‘Assume that your work ability at its best has a value of 10 points. How many points would you give your current work ability?’Confidence, measured via the Confidence after Stroke Measure [50]. This tool measures positive attitudes, confidence, and social confidence after stroke, and has established validity and reliability [51].

Research staff will receive training to ensure standardised completion of study-specific assessments. Participants and nominated carers will have the option to complete self-report questionnaires via post or online using internet-based software called QTool.

### Plans to promote participant retention and complete follow-up {18b}

Priming calls, initial and reminder letters/emails, and SMS prompts will be used to maximise data return at all timepoints. A 2-way SMS text message will also be sent (if mobile number provided) to confirm work status only of stroke survivors. If there is no response, the CTRU will alert research staff and, if possible, a blinded staff member will attempt to contact the participant via telephone or arrange a face-to-face visit to perform the assessment.

